## Abstract

Supplemental Digital Content is available in the text

## Introduction

1

Neurological diseases account for 16.8% of global deaths and about 7% of disability-adjusted life years (DALYs). Cerebral pathologies are the second cause of death worldwide.^[1]^ Neurological diseases include those of the central nervous system, such as stroke, spinal cord injury, cranioencephalic trauma, and multiple sclerosis. All these pathologies generate some level of dysfunction, which negatively affects quality of life and also incurs high medical costs.^[2–5]^

Spasticity is an incapacitating neurological disorder that can have as etiology the above-mentioned diseases among others of the upper motor neurons.^[6–8]^ Muscular dysfunctions related to spasticity are hyperactivity and hypertonicity, muscle weakness, and contractures.^[8]^ There is also an increase in energy expenditure for performance of dynamic movements, increase in the production of lactic acid and the use of muscle glycogen, and decrease in the synthesis of fatty acids.^[9]^

In addition to muscle changes, spasticity also alters cardiorespiratory and metabolic function. There is evidence of a reduction of peripheral vessel diameter in an experimental model,^[10]^ arrhythmia symptoms, increased sympathetic stimulation to the heart and of high medullary lesions, and decreased cardiac contractility.^[11]^

In the systematic review by Block et al,^[12]^ it was demonstrated by the remote monitoring method that patients with neurological sequelae are not able to perform the recommended exercise time, and have a decreased cardiorespiratory fitness in relation to the population that does not have neurological dysfunctions. This is due to the pathophysiology of the disease-altering physical inactivity through prolonged sedentary behavior.

It is well understood that aerobic physical training improves cardiorespiratory fitness in the general healthy population and also in several disease groups. The application of aerobic training in individuals with central nervous system diseases is increasing due to the benefits demonstrated in the literature, such as improvement of cognition, cardiovascular conditioning, reduction of anxiety and depression symptoms, and increased oxygen consumption efficiency.^[13–16]^

Significant evidence demonstrates that PBM Therapy directly affects mitochondrial functioning, increases microcirculation, reduces pain, decreases inflammatory processes, reduces muscle fatigue, and facilitates improvement in scarring processes.^[17,18]^

PBM Therapy is considered a noninvasive brain stimulation technique, with potential effects on brain plasticity. Phototherapy has been extensively studied and has been shown to be efficient for a variety of clinical procedures.^[19,20]^

PBM Therapy directly influences the activity of cytochrome c oxidase, an electron transport chain enzyme located on the internal membrane of the mitochondria, responsible for the uptake and absorption of light photons within the red and infrared spectra.^[21,22]^

According to Hennessy and Hamblin,^[23]^ if we want to stimulate the brain, we must radiate the laser light directly to the head, more precisely to the forehead, because there is no hair present, which can dissipate/disperse the photons of light. Radiating laser light directly to the forehead would stimulate the frontal lobes of the cortex, the area responsible for motor function, problem solving, memory, language, initiation, and impulse control.

Clinical studies in humans have demonstrated improvements in a wide range of brain functioning, such as cognitive and memory improvement, improvement of the behavioral picture, such as attenuation of depression and anxiety, and increased cortical oxygenation.^[17,24]^

We believe that the same stimulation of brain tissue, that is, the exposure of nervous tissue to PBM Therapy, could also trigger positive effects peripherally. It is proposed here that cardiorespiratory rehabilitation associated with PBM Therapy may increase performance in physical activity in people with reduced mobility.

Therefore, the aims of this trial will be to evaluate the parameters related to the function of the musculoskeletal and cardiorespiratory system and the impact of PBM Therapy on these parameters, through a rehabilitation and training program for people with reduced mobility.

## Methods

2

### Trial design

2.1

It is a unicentric, randomized, double-blind, placebo-controlled trial with 3 groups: control – only cardiorespiratory rehabilitation (CCR), cardiorespiratory rehabilitation with PBM Therapy (CR-PBM), cardiorespiratory rehabilitation and placebo PBM Therapy (CR-PlaceboPBM). The magnitude of the PBM Therapy effect will be compared statistically across groups. In total, there will be 90 patients (30 in each group). The trial will be conducted at the Clinic School of the University of Paraíba (Brazil), and the sessions will be 1 hour, twice a week for 9 weeks. Baseline, intermediate (4th week), final (9th week), and 2-month follow-up will be performed. Further details on the flowchart of the trial design are shown in Fig. 1.

**Figure 1 F1:**
[figure not shown]
Flow diagram of trial.

### Ethics

2.2

The protocol was approved by the Ethics and Research Committee of the University of Vale do Paraíba, Brazil (CAAE 94858718.3.0000.5503), and later registered in ClinicalTrials.gov (NCT03751306). All procedures will be in accordance with the WMA Declaration of Helsinki.

### Patients

2.3

Patients with reduced mobility due to acquired central nervous system neurological diseases and people with multiple sclerosis were included.

#### Inclusion criteria

2.3.1

Inclusion criteria are as follows:

(1)People with stroke, traumatic brain injury, spinal cord injury, brain tumor postoperative period, chronic nonprogressive encephalopathy, and multiple sclerosis;(2)Chronic neurological diseases, from 6 months of injury;(3)Caucasian individuals;(4)Age between 18 and 85 years;(5)Both sexes;(6)Individuals with cognition preserved;(7)Persons who are able to wander on the treadmill voluntarily or through assistance of the BrainMov Rehabilitation and Physical Activity Station;(8)Persons who make continuous and regular use of medications prescribed by the physician for the control and/or treatment of chronic diseases;(9)Persons with the release of the cardiologist for rehabilitation.

#### Exclusion criteria

2.3.2

Exclusion criteria are as follows:

(1)Persons who do not meet the inclusion criteria;(2)Active smokers;(3)Carriers of chronic respiratory diseases, such as chronic obstructive pulmonary disease, asthma and bronchiectasis;(4)patients with decompensated heart disease;(5)Obesity grade II - body mass index greater than 34.99 kg/m^2^;(6)Patients with spinal cord injury above sixth thoracic vertebra, who present with autonomic dysreflexia;(7)Patients with American Spinal Injury Association Impairment Scale A or B Impairment;(8)Patients with multiple sclerosis who are in the onset period;(9)Patients who use beta-blocking drugs;(10)Hemorrhagic encephalic vascular accident.

### Groups e sample size

2.4

The present trial will include 90 patients who will be divided randomly into 3 experimental groups:

(1)Control group (CCR): (n = 30) These individuals will receive only cardiorespiratory rehabilitation; therefore, no PBM Therapy will be applied, either real or placebo.(2)Transcranial Photobiomodulation Group (CR-PBM): (n = 30) Individuals in this group will receive PBM Therapy followed by cardiorespiratory rehabilitation.(3)Placebo Group Photobiomodulation (CR-PlaceboPBM): (n = 30) Individuals in this group will receive placebo PBM Therapy; the device will not deliver therapeutic light. Subsequently, they will receive cardiorespiratory rehabilitation.

All patients, after completing the trial, may receive PBM Therapy treatment. Thus, if there is any interest of a patient who did not receive the PBM Therapy during the trial, this will be provided after trial completion

### Randomization and blinding

2.5

The patients will be recruited from the waiting list of patients of the school clinic and medical records of the institution's former patients. Patients in all 3 groups, CCR (n = 30), CR-PBM (n = 30), and CR-PlaceboPBM (n = 30), must sign consent themselves and must have cognition preserved to participate in the trial. To see Inform consent check supplemental material.

The block randomization method will be used for 1:1:1 randomization to ensure a balanced distribution. Randomization will be attributed by calculating using computer program software.

Researchers responsible for evaluations, application of treatment protocol, and statistical analysis will be blinded to this information. The patient will also be blinded to group allocation. All involved (researchers and patients) in the trial will be instructed not to communicate or comment on which treatment they will receive other than cardiorespiratory rehabilitation. Only at the end of the trial will the identity of the groups and the final results be revealed through patient reports.

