#### Cardiorespiratory rehabilitation and photobiomodulation procedures

2.7.2

The treatment session will be divided into following 5 steps:

(1)Step 1: Initial seated rest before exercise, vital signs, and PBM Therapy.

Seated rest before exercise period should be 10 minutes. Concurrent with seated rest, vital signs should be measured followed by the PBM procedure.

Vital signs data such as systemic blood pressure, heart rate, respiratory rate, peripheral oxygen saturation, and BORG will be measured.

Group CCR will rest (seated) without PBM or placebo PBM.

Group CR-PBM will receive transcranial PBM Therapy (wavelength 810 nm laser, beam area on the skin 0.028 cm^2^, laser power 100 mW, irradiance 3.5 W/cm^2^, treatment time 30 seconds per point, energy 3 J per point, and fluence of 107.1 J/cm^2^ (Irradia, Stockholm, Sweden). The location of PBM Therapy will be in the middle cerebral arteries and the anterior cerebral artery (electroencephalogram points F7, F8, and AFz) according to the International 10–20 System of the electroencephalogram.

Group CR-PlaceboPBM will receive PBM Therapy with the device inactive. The therapist will be blinded to active or placebo mode.

After initial seated rest, vital signs data (systemic blood pressure, heart rate, respiratory rate, peripheral oxygen saturation, and BORG) will be repeated.

(2)Step 2: Aerobic training phase: (i) Warm-up, (ii) Aerobic resistance training, and (iii) Cool down.

These phases will occur on a treadmill (Moviment RT200, São Paulo, Brazil), using support of the BrainMov Rehabilitation and Physical Activity Station (Fig. 2). This is composed of 4 iron pillars, where extensors and elastic cords are added, favoring suspension and stabilization of people with mild to severe impairment of neuromuscular function. This structure allows users to practice dynamic exercises that could not be performed without the help of others. The equipment is safe and thus adapted for rehabilitation and training of people with reduced mobility, providing aerobic training and muscle strengthening.^[25]^

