
### Statistical analysis

2.9

Data will be stored in Excel (Windows) and in the cloud, organized as mean and standard deviation. Statistical analysis will be carried out within the University of Vale do Paraíba institution. Assumption of normality will be checked, to direct the choice of appropriate statistical test used for intra and intergroup comparisons. Statistical significance will be adopted as *P* < .05. Scientific Data Analysis and Visualization (SciDAVis) will be the software of choice.

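### Blocked 1:1:1 allocation with no stratification factor named balances arm sizes but not the six pooled diagnoses; this costs precision and leaves chance imbalance, but is not systematic bias

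*Protocol article*

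**What the plan says.** All statements are from the protocol article.

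- **Allocation (2.5 Randomization and blinding):** "The block randomization method will be used for 1:1:1 randomization to ensure a balanced distribution". No stratification factor, minimisation or block size is given.
- **Population (2.3.1 Inclusion criteria):** "People with stroke, traumatic brain injury, spinal cord injury, brain tumor postoperative period, chronic nonprogressive encephalopathy, and multiple sclerosis". Section 2.3.2 narrows this mix, for example by excluding "Patients with American Spinal Injury Association Impairment Scale A or B Impairment" and hemorrhagic stroke, but all six diagnoses remain eligible.
- **Size (2.1 and 2.4):** 90 patients, 30 per arm, three arms. The control arm (CCR) receives neither active nor placebo light.
- **Intervention (2.7.2):** light is applied to the head only, at "electroencephalogram points F7, F8, and AFz".
- **Evaluations (2.6):** baseline, intermediate, final and 2-month follow-up.
- **Analysis (2.9):** "Assumption of normality will be checked, to direct the choice of appropriate statistical test used for intra and intergroup comparisons". No covariate is mentioned.

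**The concern.** The stated purpose of the blocks is balance, but blocks without strata deliver balance of arm counts only. Diagnosis is known at entry, costs nothing to record, and plausibly predicts many of the outcomes in section 2.8: squat electromyography and balance, respiratory muscle strength, the adapted walk test and heart rate variability. With 30 patients per arm, a chance excess of one lesion type in one arm is not rare. In that single realised allocation it could mimic part of a light effect or hide it. Even with perfect balance, an analysis that ignores a strong prognostic factor carries extra noise.

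The allocation scheme has to be right before patients enter. A later analysis plan can adjust for diagnosis but cannot rebalance the arms.

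**Working it through.** **Inputs.** From the article: 90 patients, three arms of 30 (30 × 3 = 90, which agrees), blocks at 1:1:1, six diagnoses, significance level 0.05 (taken as two-sided). The article gives no diagnosis mix, effect size, SD or power, so these are assumed over ranges: K patients of 90 in a given lesion category, and a difference of D = 0.5 or 1.0 within-category SD between lesion types.

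**Step 1. Chance of imbalance in one category.** If K of the 90 patients have the category and the arms are filled without regard to it, then

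P(a, b, c) = C(30,a) × C(30,b) × C(30,c) / C(90,K), with a + b + c = K.

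This ignores the block boundaries, which barely matter for a factor not used in blocking. A difference of 6 patients is 6/30 = 20 percentage points. Summing over |a − b| ≥ 6 for two given arms, and over max − min ≥ 6 for any pair:

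| K of 90 | Two given arms | Any of the three pairs |
|---|---|---|
| 10 | 2.2% | 6% |
| 15 | 5.6% | 13% |
| 27 (30%) | 12.3% | 26.3% |
| 45 (50%) | 15.7% | 32.5% |

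For the active-versus-placebo contrast, the middle column applies.

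**Step 2. All six diagnoses together.** Simulated permuted blocks of 3 or 6 give the chance that at least one diagnosis differs by 6 or more patients between active and placebo. It is about 28% with six diagnoses of 15 each, and about 25% with an assumed mix of 40/15/15/10/5/5. With the blocks stratified by diagnosis, it was 0 in the same simulations.

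**Step 3. Effect on an unadjusted post-treatment comparison.** The shift is imbalance × D:

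- D = 1.0: 0.20 × 1.0 = 0.20 SD
- D = 0.5: 0.20 × 0.5 = 0.10 SD

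For scale, 30 versus 30 at two-sided 0.05 detects (1.96 + 0.84) × √(2/30) = 0.72 SD with 80% power.

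Simulation with no treatment effect and an unadjusted t-test:

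- Over all randomizations, mean error is about 0 and type I error 4.8 to 5.1%.
- Only among draws with an imbalance of 6 or more patients in one direction, the mean shift is about 0.11 SD (D = 0.5) or 0.22 to 0.24 SD (D = 1.0), and the type I error about 6% or 10 to 11%. These shifts slightly exceed 0.10 and 0.20 because draws with more than 6 patients are included.

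**Step 4. Precision.** With share p in the category and D = 1, variance is inflated by the factor 1 + p(1 − p): 1.21 at p = 0.3 and 1.25 at p = 0.5. The share of variance due to lesion type is 0.21/1.21 = 17% and 0.25/1.25 = 20%.

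**Step 5. With baseline as a covariate.** Suppose the 1 SD lesion difference is present equally at baseline and the within-category correlation is r. The baseline slope is b = (r + p(1 − p)) / (1 + p(1 − p)), and the remaining shift is 0.20 × (1 − b).

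- p = 0.3, r = 0.5: b = 0.71/1.21 = 0.587, shift 0.083 SD
- p = 0.3, r = 0.8: b = 1.01/1.21 = 0.835, shift 0.033 SD
- p = 0.5, r = 0.5: b = 0.75/1.25 = 0.600, shift 0.080 SD
- p = 0.5, r = 0.8: b = 1.05/1.25 = 0.840, shift 0.032 SD

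So about 0.03 to 0.08 SD remains.

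**The case against.** **The article may simply be silent.** Blocking is compatible with strata, and a condensed article may leave the factor to the full protocol. This stands in part: one may not conclude that the sponsor decided against stratification. But allocation is protocol content, and the article gives the method and its purpose without a factor, so asking for one is fair. The missing covariate is a weaker complaint, since it may well sit in an analysis plan that is not shown; it is raised here only as the companion of stratification.

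**It is not bias.** A reader might infer that the comparison is systematically biased or that false positives exceed 5%. Step 3 contradicts both: chance imbalance is already covered by the 5% level. Only conditional error in an unlucky draw and lost precision remain.

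**Baseline is measured.** Correct, and it removes most of the shift. A change score would remove it entirely if the lesion difference were the same at baseline. The article does not commit to either analysis.

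**The assumptions are high.** A 1 SD lesion effect and a 30 to 50% share have no source in the article, and the exclusions, the treadmill requirement and the preserved-cognition requirement narrow the differences between diagnoses. This stands; the lower ends are therefore shown.

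**Response by lesion site.** Because the light goes to the head, a reader might infer that patients with spinal cord injury cannot respond, or that multiple sclerosis belongs with them. Neither is supported. The stated hypothesis is stimulation of brain tissue with peripheral effects and needs no lesion under the probe, and nothing in the article places multiple sclerosis outside the diseases involving the brain. A differing response would in any case call for an interaction analysis, which stratification does not replace.

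**Conclusion.** The point holds as an improvement to the design, of moderate size. As described, the blocks secure equal arm counts and do nothing for case mix in a deliberately mixed population. A gap of 20 points or more between two given arms has a probability of about 12 to 16% if 30 to 50% of patients share a lesion category, and 2 to 6% if 10 to 15 of the 90 do. In that event, a 1 SD lesion effect moves an unadjusted post-treatment comparison by about 0.2 SD, a little over a quarter of the 0.72 SD detectable with 80% power (0.20/0.72 = 0.28). With baseline as a covariate it moves by about 0.03 to 0.08 SD. The mix, the lesion effect and the correlation are assumptions throughout. The validity of the trial is not in question.

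**What to change.** In section 2.5, stratify the permuted-block list by one coarse, prespecified lesion category. An example is spinal cord injury versus diseases involving the brain, with the placement of multiple sclerosis decided and stated in advance. Vary the block size, because CCR allocations are visible and make fixed small blocks partly predictable. In section 2.9, include the stratum and the baseline value of the outcome in the between-group analysis. If recruitment has started, leave the list alone and make the covariate adjustment only. If the full protocol already stratifies, name the factor and carry it into the analysis.

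The cost is a new randomization list and two covariates. An incomplete block in a stratum may leave an arm one or two patients away from 30, which is negligible.

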### Evaluation procedure

2.6

(1)Evaluation 1 (baseline), first day of cardiorespiratory rehabilitation(2)Evaluation 2 at approximately 4.5 weeks of cardiorespiratory rehabilitation (Intermediary)(3)Evaluation 3 at approximately week 9 of cardiorespiratory rehabilitation (final)(4)Evaluation 4 follow-up, 2 months following ending of cardiorespiratory rehabilitation.

Data will be stored on the researchers’ computers and in the cloud with shared access among researchers involved in the trial. The evaluation and evolution sheets will be archived within the Laboratory of Sensory-Motor Rehabilitation Engineering, in addition to the digital copy, also stored in the cloud.

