#### Safety measures

2.7.3

During PBM Therapy, patient, therapist, and any observers will wear safety laser goggles with suitable optical density for the wavelength and intensity used.

For hygiene, the laser probe tip will be cleaned up between patient applications. Vital signs and effort perception (by the scale BORG and training heart rate by the Karvonen equation) will be monitored throughout, in order to identify any changes outside normal physiological ranges. If the peripheral oxygen saturation decrease is equal to or less than 88%, the patient will be supplemented with oxygen, adjusted as necessary. An oxygen gas cylinder, nasal catheter and mask, and ready-to-use air humidification system will be available at the site.

To reduce the minimum risk of falls, in the case of dizziness, abrupt changes in vital signs, or motor function, there will always be 2 physiotherapists close to the patient to support. The treadmill will be immediately disconnected by one of the therapists, and as a preventive measure, patients will use the BrainMov Rehabilitation and Physical Activity Station equipment to maintain greater stability and suspension if they lose their balance.

Patients may discontinue treatment at any time if they feel sick or feel any discomfort.

Should a patient present worsening of any symptom caused by the therapy, it will be immediately interrupted, and if necessary, the patient will be rescued.

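### The double-blind claim cannot hold for the CCR arm, which gets no device, so a PBM effect read against CCR cannot be separated from device-contact, expectation or performance effects

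*Protocol article*

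**What the plan says.** Section 2.1 of the protocol article gives the design as follows: "It is a unicentric, randomized, double-blind, placebo-controlled trial with 3 groups". It adds: "The magnitude of the PBM Therapy effect will be compared statistically across groups".

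Section 2.5 names all three arms and then makes two blinding statements. For staff: "Researchers responsible for evaluations, application of treatment protocol, and statistical analysis will be blinded to this information". For participants: "The patient will also be blinded to group allocation". Neither makes an exception for CCR.

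Section 2.4 says of CCR: "therefore, no PBM Therapy will be applied, either real or placebo". Section 2.7.2 repeats this at session level: "Group CCR will rest (seated) without PBM or placebo PBM". In the same step CR-PBM has a laser applied at three scalp points, and CR-PlaceboPBM has the same procedure with the device inactive. Section 2.7.2 describes the therapist's blinding only as not knowing whether the device is in active or placebo mode. Section 2.7.3 adds: "During PBM Therapy, patient, therapist, and any observers will wear safety laser goggles".

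Section 2.9 refers to intra- and intergroup comparisons at P < .05 and names no particular contrast.

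**The concern.** The article claims a property for three arms that its own procedures can deliver for two. A therapist must know whether to pick up the device, so a CCR allocation is open to that therapist at the first session. A CCR patient sits through the rest period with no probe, at each of 18 sessions.

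This matters for inference as well as for labelling. Several outcomes in section 2.8 depend on effort or self-report: spirometry with maximal voluntary ventilation, respiratory pressures, peak flow, the adapted 6-minute walk test and the SF-36. On these, knowing that one has or has not had a device treatment, or being coached by someone who knows, can shift the result. A difference from CCR could then be published, under a double-blind label, as an effect of light.

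**Working it through.** **1. Who can be blinded to what.** Setting sections 2.4, 2.5, 2.7.2 and 2.7.3 side by side:

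| Contrast | Visible difference in the session | Therapist blind? | Patient blind? |
|---|---|---|---|
| CR-PBM v CR-PlaceboPBM | None described; device applied in both | Achievable | Achievable |
| CR-PBM v CCR | Device applied v seated rest only | No | In practice no |
| CR-PlaceboPBM v CCR | Device applied v seated rest only | No | In practice no |

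The therapist entries follow directly from the procedure. The patient entries need one more step: the CCR patient must know that the trial is about PBM. Section 2.4 offers PBM after the trial to anyone who did not receive it, so PBM does not appear to be hidden from participants.

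**2. Inputs for scale.** From the article: 3 arms of 30 (3 × 30 = 90, which agrees with the stated total) and a significance level of 0.05. The article does not state sidedness; two-sided is assumed. Also assumed: a light effect of zero, and a device-contact effect of *b* SD, equal in both device arms and absent in CCR. The documents give no value for *b*, so a range is shown.

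**3. CR-PBM versus CCR.** Two-sample t test with 30 + 30 − 2 = 58 degrees of freedom. The critical value is 2.002 and the noncentrality is δ = b / √(2/30) = b / 0.2582. The probability of significance is P(|T| > 2.002), where T is noncentral t with 58 df and noncentrality δ.

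**4. Three-group F test.** The arm means are (0, b, b). The noncentrality is λ = 30 × [(2b/3)² + 2(b/3)²] = 20b². There are 2 and 87 degrees of freedom and the critical value is 3.101.

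| b (SD) | δ | CR-PBM v CCR significant | λ | Three-group F significant | CR-PBM v CR-PlaceboPBM significant |
|---|---|---|---|---|---|
| 0.1 | 0.387 | 6.7% | 0.2 | 6.5% | 5% |
| 0.2 | 0.775 | 11.9% | 0.8 | 11.3% | 5% |
| 0.3 | 1.162 | 20.8% | 1.8 | 20.1% | 5% |
| 0.5 | 1.936 | 47.8% | 5.0 | 48.9% | 5% |

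A normal approximation for CR-PBM versus CCR gives nearly the same: 6.7%, 12.1%, 21.3% and 49.1%.

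**5. Why the last column stays at 5%.** Both device arms carry the same *b*, so the difference in means is b − b = 0.

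**The case against.** The strongest defence is that the design already contains the remedy. A sham arm of 30 separates light from device contact, and section 2.7.2 describes therapist blinding in exactly the terms that are achievable. A no-device arm is a legitimate addition. All of that stands: the light-versus-sham comparison is intact, and the fault lies in the scope of the blinding statement and of the planned comparison.

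A second defence is that the choice of contrast is usually left to a SAP, which is not shown. This stands in part. The article does not rank the contrasts, and a reader should not infer that it gives the CCR contrast equal standing or says a PBM claim will rest on it. But section 2.1 does present the comparison over all groups as a measure of the PBM effect, and no SAP could make the blinding statement true for CCR.

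Third, the percentages in the working are not error rates in the strict sense. If device contact has a real effect, CR-PBM and CCR truly differ, and the figures are the power to detect that difference. They become false claims only when the difference is credited to light. This is correct, and it is why the wording of the comparison matters.

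A reader might also infer that evaluators and the analyst are unblinded, because section 2.6 keeps data "in the cloud with shared access among researchers involved in the trial" and holds a digital copy of the evaluation sheets there. The documents do not support this. They do not say that the sheets record arm or device use, or that every file is open to everyone. Evaluators separate from the treating staff could remain blind, helped by the instruction in section 2.5 not to discuss treatment beyond rehabilitation.

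Nor do the documents show that expectation bias is present. It cannot be excluded in the CCR contrasts, and it is likely to matter less for outcomes such as lactate, thermography or R-R intervals.

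**Conclusion.** The point holds. The double-blind statement in sections 2.1 and 2.5 is wrong for CCR: certainly for treating therapists, and in practice for CCR patients. Any PBM effect read from CR-PBM versus CCR, or from a three-group test, is therefore confounded with device contact, expectation and performance.

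The size is unknown. Over an assumed device-contact effect of 0.1 to 0.5 SD with no light effect, the chance of a significant CR-PBM versus CCR result runs from about 7% to 48%. The low end is close to nominal; the high end is serious. The figures rest on two-sided testing at 0.05, 30 analysed per arm, and an effect equal in both device arms. The CR-PBM versus CR-PlaceboPBM contrast is unaffected as long as the sham is convincing. The statement should be corrected, because it is untrue as written and governs how the results may be described.

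**What to change.** - **Section 2.1:** limit the double-blind label to CR-PBM versus CR-PlaceboPBM. Replace the comparison over all groups with that contrast as the one supporting any claim of a PBM light effect.
- **Section 2.5:** state that CCR is open to the patient and to the treating therapist, and that the patient and therapist blinding statements apply to the two device arms.
- **Reporting:** present the CCR contrasts as secondary and open-label. CR-PlaceboPBM versus CCR estimates the effect of device contact and expectation; CR-PBM versus CCR estimates that effect plus any light effect.

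The cost is a change of wording and a narrower blinding label. Randomisation, sample size, procedures and staffing are unchanged.
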